### 4 Adverse events

Study treatment will be discontinued for all patients displaying anaphylactoid reactions (i.e. if a patient displays anaphylactoid signs after either a test dose or intramuscular dose of antitoxin, then no further antitoxin will be given regardless of treatment allocation). The occurrence of such reactions is rare (<0.5%) and reported to be lower with human than equine antitoxin
^7^. Management of adverse events will follow normal care and current practice guidelines and a standard operating procedure. As these reactions occur irrespective of route of administration, treatment does not require unblinding.

***4.1 Safety reporting***

Definitions

*Adverse Event (AE)* - is any untoward medical event that occurs to a study participant during the course of the study whether or not that event is considered related to the study drug. An AE can, therefore, be any unfavorable and unintended sign (including an abnormal laboratory finding, for example), symptom, or disease temporally associated with the study drug, whether or not considered related to the study drug.

Stable chronic conditions, such as arthritis, which are present prior to clinical trial entry and do not worsen are not considered AEs and will be documented in the subject’s clinical chart as medical history. 

Clinical or laboratory events are considered AEs only if they occur after the first dose of study treatment (see below for reporting of AEs).

*Serious Adverse Event (SAE)* - An AE is considered to be "serious" if it results in one of the following outcomes

•Death•Life-threatening event (the subject was at immediate risk of death at the time of the event; it does not refer to an event which hypothetically might have caused death if it were more severe)•Inpatient hospitalization (new admissions) or prolongation of existing hospitalization (beyond what is expected for normal clinical care)•Persistent or significant disability/incapacity (a substantial disruption of a person's ability to conduct normal life functions)•Congenital anomaly/birth defect

Any undiagnosed pregnancy during which treatment occurred will be followed until outcome. Any congenital abnormality or birth defect will be recorded as a SAE.

*Unexpected Serious Adverse Events (USAE) -* are untoward medical events which fit one or more of the criteria for SAEs above and which are not considered a part of normal clinical progression of disease or an expected reaction to standard treatment therapy. Any event that becomes of concern to the investigators or study doctors during the course of the trial may be reported as a USAE.

***4.2 Assessment of AEs.*** AEs will be graded according to the Common Terminology Criteria for Adverse Events (CTCAE) definitions
^26^. In the event that an AE is not described within the CTCAE definitions, the following generic severity grading will be used: 

•Grade 1 Mild: asymptomatic or mild symptoms; clinical or diagnostic observations only; intervention not indicated.•Grade 2 Moderate: minimal, local or noninvasive intervention indicated; limiting age-appropriate instrumental Activities of Daily Living (ADL)
^a^.•Grade 3 Severe or medically significant but not immediately life-threatening: hospitalization or prolongation of hospitalization indicated; disabling; limiting self-care ADL
^b^.•Grade 4 Life-threatening consequences: urgent intervention indicated.

[Note: “Life-threatening” as a severity grade is not necessarily the same as “life-threatening” as a “serious” criterion used to define a SAE. The former is a “potential” threat to life and the latter is an “immediate” threat to life.]

A laboratory abnormality only needs to be recorded as a clinical AE if it is associated with an intervention. Intervention includes, but is not limited to, discontinuation of a current treatment, dose reduction/delay of a current treatment, or initiation of a specific treatment. In addition, any medically important laboratory abnormality may be reported as an AE at the discretion of the investigator. This would include a laboratory result for which there is no intervention but the abnormal value suggests disease or organ toxicity. Laboratory events will be graded according to CTCAE definitions.

If clinical sequelae are associated with a laboratory abnormality, the diagnosis or medical condition should be reported as the AE (e.g. renal failure, haematuria) - not the laboratory abnormality (e.g. elevated creatinine, urine RBC increase).

The relationship of each AE to the trial medication must be determined by a medically qualified individual according to the following definitions:

•Related: The AE follows a temporal sequence from trial medication administration, follows a known pattern of response for which no other explanation is present.•Possibly related: The AE has a temporal relationship to the trial medication administration, does not follow a known pattern of response but cannot be attributed to another cause.•Not related: The AE is probably produced by the participant’s clinical state or by other modes of therapy administered to the participant.

Patients will be under active surveillance for AEs. All AEs will be scored as not related, possibly related, or related to the study drug. The events listed below, and any others agreed between the treating doctor and Principal Investigator, are recognised adverse reactions to anti-toxin may be considered related to the trial intervention: chills, fever, myalgia, moderate back pain, arthralgia, local pain and redness at injection site, itching, rash, hypotension. Rarely anaphylactic reactions may occur.

In addition AEs related to lumbar puncture procedure will include headache, bloody tap, infection, vomiting, dysaesthesia, epidural, subdural or subarachnoid hemorrhage, post dural puncture, cerebral herniation.

AEs related to intra-muscular injection will include abscess formation, tissue fibrosis, contracture, haematoma, injury to blood vessels, bones and peripheral nerves.

***4.3 AE recording.*** All AEs which initiate after administration of the first dose of study drug and before discharge from ICU will be recorded in the Case Report Form. All events judged to be possibly related or related to the trial intervention will be followed to resolution.

***4.4 Regulatory reporting of AEs.*** As SEAs and mortality are common in tetanus, safety reporting will focus on events of potential relevance to the trial intervention. The following SAEs will be reported to the relevant ethics committee:

•All unexpected SAEs•All SAEs judged to be related or possibly related to the trial intervention•All deaths or life-threatening events

The above SAEs will be reported as soon as possible but within 24 hours of the time of acknowledgement of the SAE to the site ethics committee.

An initial written report will be sent as soon as possible but not later than 7 days from the acknowledgement of the event. The format and content of the initial report should follow the Viet Nam Ministry of Health Ethics Committee report template and include all information available at the time of reporting. A follow up report with complete details will be sent within 15 days since the time of acknowledgement if the initial report does not contain the details of event resolution.

All SAEs that do not meet criteria above will be included in the annual report to the Ministry of Health EC Viet Nam.

***4.5 Safety reporting and the Data Safety and Monitoring Board.*** An independent Data and Safety Monitoring Board will be established consisting of expert Vietnamese and international researchers and doctors, with the necessary clinical, research and statistical knowledge. The Data and Safety Monitoring Board will review the protocol and agree to a data review schedule and reporting requirements applicable before the study commences, with particular reference to the details of the interim review. A Data and Safety Monitoring Board charter will outline its responsibilities and how it will operate.

The DSMB will perform a safety review of data for the first 20 patients enrolled to the trial. This review will include unblinded summary tables of baseline characteristics, SAEs, AEs and event reports submitted to the DSMB. An analysis of overall clinical outcome will be performed. An annual safety review will be performed and, if deemed necessary, an additional safety review may be performed after the enrolment of 60 patients or other interval at the discretion of the Data and Safety Monitoring Board based on available data and ongoing reporting. All Data and Safety Monitoring Board reports will be sent to the responsible ethical committees including the site ethics committees, the Oxford Tropical Research Ethics Committee and the Viet Nam Ministry of Health ethics committee for consideration. Recruitment will continue during the Data and Safety Monitoring Board review period. 

As the dissemination of preliminary summary data could influence the subsequent conduct of the trial and introduce bias, access to interim data and results will be confidential and strictly limited to the Data and Safety Monitoring Board members. No results (except for the recommendation) will be communicated to the outside and/or the clinical investigators involved in the trial.

***4.6 Protocol violations.*** Protocol violations are events that contradict or omit protocol instructions and fulfil one or more of the following criteria: 1) the safety/welfare of one or more patients is put at risk by the non-compliance, 2) the integrity of study data is compromised by the violation.

Protocol violations must be reported to the sponsor as soon as possible. If the principal investigator or sponsor confirms that the violation poses a risk to patient safety/welfare or the integrity of study data, the protocol violation must be reported to the responsible hospital Ethics Committee.

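### The causality definitions in section 4.2 give no fitting class to an adverse event that matches a known reaction but may also have another cause

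*Protocol article*

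**What the plan says.** Section 4.2 makes the definitions binding: "The relationship of each AE to the trial medication must be determined by a medically qualified individual according to the following definitions". In addition to timing, the three classes require the following.

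- *Related*: the event "follows a known pattern of response for which no other explanation is present".
- *Possibly related*: the event "does not follow a known pattern of response but cannot be attributed to another cause".
- *Not related*: "The AE is probably produced by the participant’s clinical state", or by other treatment.

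The same section allows no fourth class: "All AEs will be scored as not related, possibly related, or related to the study drug". It then lists recognised antitoxin reactions ("chills, fever, myalgia, moderate back pain, arthralgia, local pain and redness at injection site, itching, rash, hypotension") and says that these may be considered related to the trial intervention. Separate lists follow for events related to lumbar puncture and to intramuscular injection.

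The class has two consequences. Section 4.3 states: "All events judged to be possibly related or related to the trial intervention will be followed to resolution". Section 4.4 names three groups of serious events for reporting within 24 hours, and one of them is "All SAEs judged to be related or possibly related to the trial intervention". The other two groups are unexpected serious events, and deaths or life-threatening events. All remaining serious events go into the annual report.

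**The concern.** A three-level causality scale should put uncertain cases in the middle. Here the middle class is closed to any event that resembles a recognised reaction. When the cause is uncertain, looking like a known antitoxin reaction removes the event from *possibly related*, where one would expect the opposite.

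The overlap is realistic in this trial. Hypotension is on the antitoxin list in section 4.2, and it is also among the complications that section 8.3 hopes treatment will reduce. Infection is on the lumbar-puncture list, while section 8.3 also names hospital-acquired infection as a complication. Fever in intensive-care patients with tetanus is a further plausible case.

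What is at stake is the handling of individual safety events in what the Discussion describes as the first study of intrathecal antitoxin in Vietnam. Two assessors could score the same event at opposite ends of the scale, and both could cite section 4.2.

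**Working it through.** No arithmetic applies. The check is to take an event with suitable timing and test it against each definition. It is classed by whether it follows a known pattern and by how strong the competing explanation is.

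| Known pattern? | Other explanation | *Related* | *Possibly related* | *Not related* | Result |
|---|---|---|---|---|---|
| Yes | None | met | fails (known pattern) | fails | *Related* |
| Yes | Possible, not probable | fails (another explanation exists) | fails (known pattern) | fails (not probable) | **no class fits** |
| Yes | Probable | fails | fails | met | *Not related* |
| No | None | fails (no known pattern) | met | fails | *Possibly related* |
| No | Possible, not probable | fails | depends on how attribution to another cause is read | fails | *Possibly related*, or unclear |
| No | Probable | fails | fails | met | *Not related* |

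Three points follow.

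1. In the three rows with a known pattern, *possibly related* is never available, whatever the competing explanation.
2. In the second row no definition is met. A class must still be chosen, so the assessor can reach *not related* by elimination, against that class's own requirement that another cause be probable.
3. For the same row, the antitoxin list lets the assessor choose *related*. That sets aside the condition that no other explanation be present, and it still does not open the middle class.

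The consequence can be traced for a second-row event scored *not related*. Section 4.3 no longer requires follow-up to resolution. If the event is serious, it leaves the 24-hour route only if it is also not fatal, not life-threatening and not unexpected. Section 4.1 treats as unexpected only what is not part of normal disease progression or an expected reaction to standard treatment. An event put down to tetanus, for example one that prolongs the hospital stay, can therefore miss that trigger as well and go to the annual report.

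There is also a difference in scope. The definitions speak of trial medication and the scoring sentence of the study drug, while sections 4.3 and 4.4 act on the trial intervention. The lumbar-puncture and injection lists concern procedures, which the definitions do not mention.

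**The case against.** The strongest reply is that the damage is small and partly repaired by the text itself.

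- *Not related* requires that another cause be probable, so no rule sends these events there. This stands. The defect is an event without a fitting class, and *not related* is only one way that an assessor may resolve it.
- Section 4.2 itself lets listed reactions count as related, and the lumbar-puncture list is worded more firmly still. This stands as a possible route. It does not remove the problem, because the definitions are mandatory and contradict it.
- Safeguards exist. All adverse events from first dose to ICU discharge are recorded (4.3). Deaths, life-threatening events and unexpected serious events are reported whatever their class (4.4). Any event of concern may be reported as unexpected (4.1). The monitoring board sees unblinded adverse-event tables for the first 20 patients and reviews safety annually (4.5). Patients are followed to 240 days for death and disability (section 2). All of this stands and limits the effect.

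A reader might also infer that the definitions undermine the human-versus-equine comparison by driving related-event rates towards zero. The documents do not support that. The endpoint in section 2.2 is incidence of adverse events with no relatedness filter, section 1.2 asks only for data to inform the choice of product, and section 5.2 compares randomised arms. Nor do the documents show that the problem case is the usual one. They give no frequency for it. For several listed reactions, such as itching, rash and injection-site pain, they state no tetanus explanation, and section 8.3 puts side effects of equine antitoxin at the hospital below 1%.

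**Conclusion.** The point holds as a defect in a stated rule. The definitions in section 4.2 do not classify an event that matches a known reaction and has a possible other cause, and they conflict with the list of recognised reactions in the same section. This follows from the wording alone. It assumes only that the definitions are applied as written and that one of the three classes must be chosen, both of which the section says.

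The effect is confined to three things: follow-up to resolution under 4.3; 24-hour reporting under 4.4 of expected serious events that are neither fatal nor life-threatening; and any tabulation by relatedness. If assessors resolve the gap by choosing *not related*, counts of related or possibly related events would be too low, by an amount the documents cannot give. The primary analysis, the all-AE incidence endpoint, the randomised human-versus-equine comparison, and the reporting of deaths, life-threatening events and unexpected serious events are unaffected.

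**What to change.** Replace the middle definition in section 4.2 with wording such as: *Possibly related: the event has a temporal relationship to trial medication or a study procedure and a causal role cannot be excluded, whether or not it follows a known pattern and even if another explanation is possible.*

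Keep *not related* for events that are probably due to another cause or whose timing is implausible. Extend the other definitions to study procedures as well. Then align the three lists in section 4.2 with the definitions, by stating that listed reactions are scored under them and are not automatically related or unrelated.

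The cost is one definition, a matching sentence for the lists, and the case report form guidance. The downside is that somewhat more events will be expedited and followed to resolution. Section 12 says recruitment has begun, so events already scored would need re-scoring under the new wording, blind to allocation, if relatedness is to be tabulated consistently.

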Current treatment for tetanus in Vietnam consists of intramuscular equine antitoxin. One randomized controlled trial has compared equine antitoxin in the treatment of tetanus with human antitoxin (human tetanus immunoglobulin) in a total of 130 neonates. There was no difference in complications and no side effects attributable to antitoxin were apparent in either group
^23^. Currently in Vietnam, human antitoxin is more expensive and is only just becoming available, although it is the product recommended by the World Health Organization due to a theoretical improved side-effect profile (with a reduced risk of serum sickness and anaphylactic reactions)
^7,
24^. Better understanding of the side-effect profile and use of human versus equine preparations would be useful in Vietnam and many low and middle income countries when choosing which preparation to use. 

The primary aim of this study is to assess the benefit of additional intrathecal tetanus antitoxin to intramuscular regimens. However, due to the factorial design of this study, we are also able to compare the side effect profile of equine and human antitoxin.

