•The attending doctors will contact the independent study doctor (see below) when a patient has entered the study. The independent study doctor who does not have normal duties on the ICU nor responsibility for day-to-day care of tetanus patients will access the treatment pack and allocation to ascertain whether the additional intrathecal injection or a sham procedure is to be performed.•The independent study doctor or a similarly independent study nurse will deliver the initial intramuscular injection of antitoxin, thus doctors and nurses treating patients will not be aware of initial intramuscular treatment.•The intrathecal injection or sham procedure will be given by the independent doctor behind screens. The sham procedure will involve placing a dressing over the lumbar area in an identical way to the procedure after true lumbar puncture. In this way doctors and nurses treating the patient will not be aware of the intrathecal treatment. Patients will be asked not to discuss their given treatment with doctors or nurses caring for them.•All patients will be kept in the supine position for 4 hours after intrathecal injection or sham procedure, in keeping with normal procedure following lumbar puncture. Supine position of tetanus patients has been shown to be non-inferior to semi-recumbent
^25^, therefore we do not think this is deleterious to patient care.•No open record of the lumbar puncture procedure or study drug administered will be kept in the clinical notes. A sealed record of the intrathecal injection procedure will be placed in a sealed envelope in the patients notes to be opened if the attending clinicians feel necessary.•Daily management decisions will be made by attending doctors (responsible for day-to-day patient care) following normal protocols and using defined criteria for mechanical ventilation.

***3.9 Baseline assessment.*** This will consist of basic clinical and demographic data, including SOFA score and Tetanus Severity Score. If a wound is present swabs will be taken for
*Clostridium tetani* culture. This will provide supportive data for the diagnosis of tetanus. Bacterial DNA may be stored for later analysis.

Cerebrospinal fluid (CSF) that has been withdrawn for antitoxin administration will be stored for analysis of tetanus toxin and antitoxin concentration.

Residual samples from these analyses may be stored for use in future studies.

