### 8 Ethics

***8.1 Ethical and regulatory guidelines.*** The Principal Investigator will ensure that this study is conducted in accordance with the principles of the Declaration of Helsinki (Seoul 2008) and the terms of approval of the appropriate ethics committees. The Investigator will ensure that this study is conducted in full conformity with relevant regulations and with the International Council for Harmonization for Good Clinical Practice July 1996.

***8.2 Ethical review.*** This protocol and all associated informed consent forms has been approved by the Ethics Committee of the Hospital for Tropical Diseases (816/QD BVBND), Oxford Tropical Research Ethics Committee
^16,
17^ and the Viet Nam Ministry of Health (1122/QD-BYT). The investigators will submit and obtain, where necessary, approval from the above parties for all substantial amendments to the original approved documents.

***8.3 Risks and benefits.*** All patients will receive the best available standard-of-care in Vietnam. Side effects associated with the use of equine anti-toxin at the Hospital for Tropical Diseases are infrequent (< 1%). Human immunoglobulin is reported to be associated with an improved safety profile compared to equine preparations
^26^.

Risks of procedures involved in the study

Risk of intramuscular injection (all groups), which are minimal. All tetanus patients currently receive intramuscular injection of antitoxin; therefore there is no additional risk associated with participating in this study. Intramuscular injection of human antitoxin is reported to be associated with fewer adverse reactions than the current standard equine antitoxin.

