## Discussion

Tetanus is a vaccine preventable disease that remains a significant health problem mainly in remote or low-resource settings with limited access to modern intensive care facilities
^2,
6^. Currently in these settings mortality from tetanus remains high, and simple but effective interventions are very much needed. Due to the ubiquitous nature of
*Clostridium tetani,* the causative organism
*,* complete disease eradication is not possible and unvaccinated populations will continue to contract the disease throughout the word. As even in well-resourced settings, tetanus is associated with high healthcare costs, prolonged ICU stay and long-term disability; effective treatments that can shorten hospital stay and reduce healthcare costs are still needed. We are carrying out this study as we believe intrathecal antitoxin is an intervention with the potential to benefit all patients with tetanus and can be performed in most settings.

This is the first study of intrathecal antitoxin in Vietnam and we have focused on safety at all stages of this study. Prior to embarking on this randomized controlled trial, a pilot study was performed in which 5 patients were treated with open-label human antitoxin intramuscularly and intrathecally. These patients were recruited sequentially and new patients were only enrolled after previous patients were discharged, and clinicians and the trial Data and Safety Monitoring Board were satisfied it was safe to continue. The pilot study results, including all AEs were reported to the trial DSMB, Hospital for Tropical Diseases Ethics Committee and the Ministry of Health Viet Nam Ethics Committee and permission to proceed obtained before enrolment in the randomized controlled trial was commenced. Whilst previous studies have reported reassuringly few AEs associated with administration of intrathecal antitoxin, patients in this study will be followed carefully daily by study physicians and nurses for any evidence of AEs. Furthermore patients will be followed up 240 days after discharge from hospital.

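### Non-serious adverse events are recorded only until ICU discharge, so the window varies by patient and could be shorter in the intrathecal arm; the expected effect is small and a fixed window is cheap

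*Protocol article*

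**What the plan says.** Section 4.3 (AE recording) governs what is entered on the Case Report Form: "All AEs which initiate after administration of the first dose of study drug and before discharge from ICU will be recorded". Events judged related or possibly related are then followed until they resolve. That extends the follow-up of recorded events but not the period in which a new event counts. The AE definition in section 4.1 is wider and covers the whole course of the study.

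AE incidence is a secondary endpoint (section 2.2). The safety of intrathecal Tetagam-P and the choice between human and equine antitoxin are secondary objectives (section 1.2). On the product comparison, the Introduction says "we are also able to compare the side effect profile of equine and human antitoxin" and gives as the reason to expect a difference a "theoretical improved side-effect profile (with a reduced risk of serum sickness and anaphylactic reactions". Section 4.2 adds local reactions: "AEs related to intra-muscular injection will include abscess formation, tissue fibrosis, contracture, haematoma".

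After ICU discharge, the article provides for:

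- diazepam doses (section 3.10);
- disability and death to day 240 (section 2);
- SAE reporting that is not expressly tied to the ICU stay (section 4.4);
- a discretionary route in section 4.1: "Any event that becomes of concern to the investigators or study doctors during the course of the trial may be reported as a USAE";
- funding of readmissions for treatment-associated AEs, and of follow-up visits (section 8.4).

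The Discussion says "patients in this study will be followed carefully daily by study physicians and nurses for any evidence of AEs". It does not say for how long, and it does not change what section 4.3 enters on the form.

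**The concern.** The recording window has no fixed length; it ends when the patient leaves ICU. This matters in two ways.

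First, a patient who leaves early has only a few days in which a non-serious reaction can be recorded. If reactions such as serum sickness, abscess or contracture tend to appear after that, some will be missed in every arm.

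Second, shorter ICU stay is one of the effects sought for intrathecal treatment, and section 5.1 claims 88% power for a 25% reduction. If the treatment works, its arm is watched for less time, and part of any apparent safety advantage on late reactions would come from the shorter window.

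This is a rule about data collection, so an analysis plan cannot repair it. Section 5.2 uses ICU duration as an offset for infection, antibiotic and autonomic rates and does not list AEs there. Even if it did, an offset would not recover events that were never recorded.

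**Working it through.** **Inputs from the article.** ICU stay: median 13 days, quartiles 4 and 22 (section 5.1, 111 historic admissions; the quartiles are printed as superscripts and are read here as 4–22). Reduction considered: 25% (section 5.1). Patients: 272, hence 136 per level of each factor, and at most 136 receiving each product because some will have the intramuscular dose omitted. Equine side effects at the hospital (section 8.3): "Side effects associated with the use of equine anti-toxin at the Hospital for Tropical Diseases are infrequent (< 1", that is, below 1%.

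**Assumptions not in the article.** Delayed onset between day 7 and day 14; stay under intrathecal treatment equal to 0.75 times sham stay; the AE risks marked below as assumed.

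**Step 1. Share already out of ICU, F(t), by linear interpolation between quartiles.**

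Sham, quartiles 4 / 13 / 22:
- F(7) = 0.25 + 0.25 × 3/9 = 0.333
- F(10) = 0.25 + 0.25 × 6/9 = 0.417
- F(14) = 0.50 + 0.25 × 1/9 = 0.528

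Intrathecal, quartiles × 0.75 = 3 / 9.75 / 16.5:
- F(7) = 0.25 + 0.25 × 4/6.75 = 0.398
- F(10) = 0.50 + 0.25 × 0.25/6.75 = 0.509
- F(14) = 0.50 + 0.25 × 4.25/6.75 = 0.657

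**Step 2. Apparent risk ratio for a late reaction with equal true risk:** (1 − F intrathecal) / (1 − F sham).
- Day 7: 0.602/0.667 = 0.90
- Day 10: 0.491/0.583 = 0.84
- Day 14: 0.343/0.472 = 0.73

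Weibull, gamma and log-normal curves fitted to the three quartiles give sham F(7) of 0.32–0.33 and F(14) of 0.57–0.58, with ratios of 0.84–0.87 and 0.74–0.75. They fit the lower quartile loosely (5.2 to 5.7 days against 4).

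The historic cohort may include the 4–6% without generalized tetanus. If these were all the shortest stays, (F − d)/(1 − d) gives 0.306 and 0.508 for d = 0.04, and 0.291 and 0.498 for d = 0.06, so little changes.

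**Step 3. Human versus equine.** Expected reactions at 1%: 136 × 0.01 = 1.36 per product at most. Lost: 1.36 × 0.333 = 0.45 (day 7) to 1.36 × 0.528 = 0.72 (day 14). The expected ratio between products is unchanged unless the product itself alters ICU stay.

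**Step 4. Intrathecal versus sham, in events per 136.**

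| True late risk (assumed) | Onset | Sham recorded | Intrathecal recorded |
|---|---|---|---|
| 1% (1.36 events) | day 7 | 0.91 | 0.82 |
| 1% (1.36 events) | day 14 | 0.64 | 0.47 |
| 5% (6.8 events) | day 7 | 4.5 | 4.1 |
| 5% (6.8 events) | day 14 | 3.2 | 2.3 |

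**Step 5. Any AE.** Let e be the risk of an early AE captured in both arms and l the late risk. The ratio is [e + (1 − e) l (1 − F intrathecal)] / [e + (1 − e) l (1 − F sham)]. For e from 20% to 80% and l from 1% to 10% (both assumed), the lowest value is at e = 0.2, l = 0.10, day 14: (0.2 + 0.08 × 0.343)/(0.2 + 0.08 × 0.472) = 0.96. At e = 0.5, l = 0.05, day 14, it is 0.99. The range is 0.96–1.00.

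**The case against.** The strongest case against is about size. The secondary endpoint is overall AE incidence, and step 5 hardly moves it. The late events that do move are too few to carry a safety conclusion: at 1% the gap between arms is below 0.2 of an event, and at an assumed 5% it is 0.4 to 0.9. The late reactions that the article names are product or injection reactions, which bear on human versus equine, where randomisation keeps the loss balanced. No late reaction specific to the intrathecal route is named. Onset times are not given. Clinically important late reactions reach the SAE or USAE route, and a full Case Report Form may hold more than the article shows. All of this stands as to size. It does not change the rule in section 4.3, and none of the other routes provides for routine recording of a new non-serious event after ICU.

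Three stronger readings are tempting, and the article supports none of them:

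- **Safety data stop at ICU discharge.** They do not, because serious events, events of concern, death and disability continue to be captured.
- **The human versus equine comparison is biased.** A balanced loss costs events and precision and does not shift the contrast, unless the product changes ICU stay.
- **Intrathecal treatment will look substantially safer overall.** With a constant AE hazard of 0.05 per day, the recorded proportions would be about 46–47% sham against 38–40% intrathecal, a ratio of 0.84–0.85. The article gives no daily AE rate. To call the whole difference an artefact also requires that hazard to continue unchanged after patients leave ICU.

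The remedy also has a weakness. The sham is only a dressing, and section 3.8 says "Patients will be asked not to discuss their given treatment with doctors or nurses caring for them", so patients may know whether they had a lumbar puncture. Self-report after discharge could then differ between intrathecal and sham.

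**Conclusion.** The point holds as a minor design weakness. Non-serious AEs that start after ICU discharge can go unrecorded. The window has closed for about 25% of patients by day 4 and 50% by day 13, if trial patients resemble the historic cohort.

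The under-count would fall more heavily on the intrathecal arm only if that treatment shortens ICU stay. At a 25% reduction the apparent risk ratio for late reactions alone would be about 0.90 (day 7) to 0.73 (day 14). If AEs mostly start early, overall AE incidence would change little, and human versus equine would lose fewer than one expected reaction per product.

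That serum sickness or the listed injection reactions appear late is an assumption, and every ratio above depends on it. The case for change rests on low cost and on the place of AE incidence among the secondary endpoints, more than on the expected size of the error.

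**What to change.** Record AEs over one fixed window from first dose in every patient, for example 28 days (the length is a suggestion). Use ward records while the patient is in hospital and, for those already home, one short structured contact by a blinded member of the existing study team, with the same questions in all arms. Restrict post-ICU collection to the reactions listed in section 4.2. Compare AE proportions over the fixed window, report objective signs (rash, fever, abscess, contracture) separately from self-reported symptoms, and keep the ICU-only table alongside.

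Apart from deaths and withdrawals, this equalises observation time by design. The cost is about one contact per patient who has left ICU, in a trial that already records diazepam after ICU and follows patients to day 240. Possible differential self-report for intrathecal versus sham remains; separate reporting of objective signs limits it but does not remove it.
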